# Effects of a multi-modal static and dynamic balance and hand function training program on multi-dimensional balance ability, hand function, and life-space mobility in rural older adults: protocol for a randomized controlled trial

**DOI:** 10.1186/s13102-025-01214-2

**Published:** 2025-07-02

**Keywords:** Health intervention, Exercise program evaluation, Aging-related mobility improvement, Balance ability

## Abstract

**Background:**

Rural older adults face an increasing number of health challenges. While balance training is beneficial, it is often included as part of broader exercise programs. However, comprehensive studies specifically combining balance training with hand function training for rural older adults remain scarce.

**Objective:**

This study aims to investigate whether a combined balance and hand training program can provide programmatic references and empirical evidence for improving functional outcomes in rural older adults.

**Methods:**

A single-blind, four-group parallel, multicenter randomized controlled trial was used. Four rural communities in Huzhou, Zhejiang Province, were included in the study, with an estimated total sample size of 132 individuals. During the 16-week intervention period, the comprehensive exercise program consisted of two balance training programs and one hand training session provided by a multidisciplinary team including physiotherapists, sports professionals, nurses and community health workers. The four rural communities were randomly divided into four experimental groups in the ratio of 1:1:1:1 (a) static balance training combined with hand training; (b) dynamic balance training combined with a hand training program; (c) multi-modal static-dynamic balance and hand function training (M-mBHF) program; and (d) a Daily activity group. The multidimensional balance ability, hand function, and life-space mobility of the four parallel groups will be assessed at baseline (T0), 8 weeks of intervention (T1), 16 weeks of intervention (T2), and at 24 (T3) and 32 weeks (T4) follow-up.

**Conclusion:**

This study protocol proposes a M-mBHF program hypothesized to improve multi-dimensional balance ability, hand function, and life-space mobility in rural older adults. The anticipated outcomes aim to provide empirical evidence for future interventions targeting this population.

**Trial registration:**

Registered in the Chinese Clinical Trial Registry on 02/17/2025 (ChiCTR2500097310).

**Supplementary Information:**

The online version contains supplementary material available at 10.1186/s13102-025-01214-2.

## Introduction

With the evolution of the global population structure, it is projected that the number of older adults aged 60 and above will double to 2.1 billion by 2050. In 2024, the World Health Organization (WHO) highlighted that environmental factors have significantly impacted the health of older adults, particularly in rural areas of developing countries, where environmental limitations and rapidly rising living costs exacerbate challenges [1]. As of 2024, China’s older adults aged 60 and above have reached 310 million, accounting for 22.0% of the total population. Notably, rural areas face a more pronounced aging issue, with 23.81% of the population being older adults significantly higher than in urban areas [2]. 

Rural older adults often encounter more severe issues regarding access to health services and resources [3], leading to a higher likelihood of physical decline [4]. Long-term agricultural labor can accelerate the degradation of skeletal muscle function, impair balance, and increase fall risks due to complex terrains and limited health awareness. Data indicate that the fall mortality rate among rural older adults (9.95/100,000) is notably higher than in urban areas (7.18/100,000).[5] Studies show that older adults exhibit slower reactive abilities in fingers and arms, contributing to reduced grip strength compared to younger adults [6]. Additionally, long-term manual labor results in hand muscle strain, rough skin, and decreased tactile sensitivity, further compromising grip stability. Therefore, focusing on balance and hand function is crucial for promoting healthy aging in rural older adults.

Life-space mobility (LSM) is a comprehensive and dynamic measure that reflects the interaction between individual functions, environment, and society [7]. Compared to laboratory-based assessments, LSM provides a more accurate reflection of real-life physical activities and functions, serving as a strong predictor of adverse outcomes such as falls, hospitalization, and premature death [8]. According to the Webber framework, physical performance, including strength and balance, significantly influences LSM [9]. Kuspinar et al. found that lower walking speed, TUG test scores, and grip strength are associated with reduced LSM [8]. Uchida et al. confirmed that psychological factors, such as fear of falling, depression, and anxiety also impact LSM [10], while poor infrastructure, uneven sidewalks, and noisy traffic in rural areas contribute to mobility disorders, restricting life-space mobility [11]. 

Somatic balance ability encompasses static/dynamic steady-state balance, active balance, and reactive balance [12]. Static balance training involves maintaining independent static postures and low-intensity stability exercises. Ni’s research demonstrated significant improvements in SPPB and One Leg Stand Test scores among community-dwelling older adults after sensory-based static balance training [13]. Granacher et al. reported that an 8-week home-based static gait balance program enhanced active balance and lower limb strength in healthy older adults individuals aged 60-72 [14]. Dynamic balance training aims to improve high-intensity stability and coordination. Hagovska et al. observed significant improvements in walking speed, step length, and body posture control after ten weeks of dynamic balance training [15]. While both static and dynamic training improves balance, their combined effect on multidimensional balance and LSM remains understudied.

Despite WHO recommendations for at least 2.5 h of moderate physical activity per week for adults, rural older adults (≥ 65 years old) still have the highest sedentary time [16]. Rural older adults lacking scientific guidance, often neglect functional balance improvement. Given this context, this study, based on the environmental conditions of rural areas and the characteristics of the older adults’ physical functions (balance ability and hand function) in rural areas, attempts to open a novel M-mBHT program to address potential gaps in current interventions. The objectives of this study are as follows: (1) To construct a scientifically feasible comprehensive intervention plan combining static-dynamic balance training and hand training, promoting the application and dissemination of the intervention plan in rural community older adults; (2) To provide theoretical references for investigating the hypothesized short-term and long-term effects of comprehensive multi-dimensional balance ability, hand function, and life-space mobility for rural older adults.

## Methods

### Study design and ethical consideration

A multi-center, four-arm, parallel-group, assessor-blind randomized controlled trial and will take place in four rural communities of Huzhou City, northern Zhejiang, China. The study plan is designed to include three intervention groups: (a) static balance training combined with hand training; (b) dynamic balance training combined with hand training; (c) combined static and dynamic balance training with hand training; and control group (physical and health education).The study process is illustrated in Fig. 1. This study adheres to the CONSORT statement and SPIRIT guidelines [17, 18]. The primary or secondary outcomes were not expected to change during the course of the study. All results were specified in the protocol registered in the Chinese Clinical Trial Register (ChiCTR2500097310). It has been approved by the Medical Ethics Committee of Huzhou University (approval number: 202412-05).

**Fig. 1 Fig1:**
[figure not shown]
Study design flow chart

### Participants

Eligible participants for the trial are older adults residing in rural areas. Inclusion Criteria: (1) Age ≥ 60 years; (2) Independent walking ability for ≥ 15 consecutive minutes; (3) No communication barriers; (4) Long-term rural resident (≥ 1 year); (5) Normal or corrected-to-normal visual and hearing acuity (e.g., using glasses/hearing aids); (6) Provided informed consent and willingness to cooperate.Exclusion Criteria: (1) Untreated mental illness; (2) Concurrent participation in related sports training/drug trials; (3) Inability to adhere to the intervention protocol.

### Recruitment and informed consent

Recruitment flyers were distributed by two trained investigators through community centers and local health clinics, and individuals meeting the inclusion criteria were invited to sign informed consent forms. Additionally, local community health workers assisted in referring potential participants to the study. Interested seniors could contact the study investigators, who would explain the research and assess eligibility through telephone or face-to-face interviews.

### Sample size

Based on a previous study evaluating the impact of proprioceptive balance training on posture control in older adults [19], G*Power 3.1 was used for power analysis to determine the required sample size for detecting a statistically significant effect of the intervention [20]. The significance level (α) was set at 0.05, and the statistical power was set at 0.80. To account for an anticipated 10% dropout rate over the 16-week study period, 33 participants will be recruited per group.

### Randomization, allocation concealment, and blinding

Four rural communities in Huzhou, Zhejiang Province, were randomly selected to ensure comparability regarding economic development, cultural practices, and infrastructure. A minimum separation distance of 5 km between communities was maintained to minimize contamination risk. The investigator prepared slips labeled “Intervention groups (a)(b)(c)” and “control group” and placed them in sealed envelopes. Representatives from the four communities randomly selected envelopes and were assigned to the four groups on a 1:1:1:1 ratio. Research assistants received intervention information via sealed envelopes, while outcome evaluators and data analysts remained blinded to the intervention details. Due to the nature of the intervention, blinding participants was not feasible.

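### With one community per arm, treatment is inseparable from community, so the participant-level alpha of 0.05 and 80% power are not supported

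*Protocol article*

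**What the plan says.** The Abstract (Methods) states: "The four rural communities were randomly divided into four experimental groups in the ratio of 1:1:1:1". The section Randomization, allocation concealment, and blinding gives the mechanism: "Representatives from the four communities randomly selected envelopes and were assigned to the four groups on a 1:1:1:1 ratio". It adds that "A minimum separation distance of 5 km between communities was maintained to minimize contamination risk", which fits whole communities being the units. Nowhere does the article describe randomization of individuals.

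The only protection offered against differences between the communities is that they were "randomly selected to ensure comparability regarding economic development, cultural practices, and infrastructure".

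Study design and ethical consideration nevertheless describes "A multi-center, four-arm, parallel-group, assessor-blind randomized controlled trial", with no mention of cluster allocation. Sample size states: "The significance level (α) was set at 0.05, and the statistical power was set at 0.80", and then: "To account for an anticipated 10% dropout rate over the 16-week study period, 33 participants will be recruited per group". Dropout is the only inflation mentioned. Data analysis plans generalized estimating equations (GEEs) with group and time factors, tested at p < 0.05, and names no community term.

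**The concern.** The unit allocated is the community, but the sample size and significance level are set as if the unit were the person. With one community in each arm, arm and community are the same variable. Anything that makes one community change differently from another over the 32 weeks is indistinguishable from the effect of the program. The weekly guided group session, a separate WeChat group for each arm and the neighbourhood exercise groups mentioned in the Discussion all make shared, community-specific change plausible.

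Random selection does not make four single communities comparable. Being multi-centre does not help either, because no centre contains more than one arm and there is no within-centre comparison.

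At stake is the trial's main claim. A significant group-by-time interaction could come from community-specific change alone and could not be attributed to the combined program. If communities differ in change at all, individual-level standard errors for arm contrasts are too small.

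**Working it through.** **Inputs from the article.** Four communities; four arms; 1:1:1:1 by community; alpha 0.05 (taken as two-sided); power 0.80; 33 recruited per arm; 10% dropout; 132 in total.

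**The plan's own figure.** 4 × 33 = 132 agrees. Evaluable per arm: 33 × 0.9 = 29.7, so m = 30 is used below. The base sample size cannot be reproduced, because the article gives no effect size, SD or test family. Solving backwards, 30 per arm gives 80% power in a two-sample t test at d = 0.736. That value is an inference, used only as a reference effect.

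**Step 1, needing no assumption.** Degrees of freedom for communities within arms = 4 − 4 = 0. The between-community variance cannot be estimated.

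**Step 2, the test that the randomization itself supports.** There are 4! = 24 possible allocations. For one contrast, such as arm (c) against arm (d), the two most different communities fall in those two arms in 2 × 2 = 4 of the 24. The smallest attainable two-sided p is 4/24 = 1/6 = 0.167, and one-sided it is 2/24 = 0.083. A global four-arm statistic is unchanged by relabelling, so its randomization p is always 1. Nothing can reach p < 0.05.

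**Step 3, size under an assumed ICC of change.** The article gives no ICC; the range 0.01 to 0.10 is an assumption.

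- Design effect: DE = 1 + (m − 1) × ICC. For ICC 0.05: 1 + 29 × 0.05 = 2.45.
- Effective n per arm: 30/DE.
- Pairwise type I error: 2 × [1 − Φ(1.96/√DE)]. For ICC 0.05: 1.96/√2.45 = 1.252, giving 0.21.
- Four-arm test on a single change score: P(χ² with 3 df > 7.815/DE).
- Power if the ICC were known: two-sample t test at d = 0.736 with the effective n.

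| ICC | DE | Effective n per arm | Type I, pairwise | Type I, four-arm | Power |
|---|---|---|---|---|---|
| 0 | 1.00 | 30 | 5% | 5% | 80% |
| 0.01 | 1.29 | 23 | 8% | 11% | 69% |
| 0.02 | 1.58 | 19 | 12% | 18% | 60% |
| 0.05 | 2.45 | 12 | 21% | 36% | 41% |
| 0.10 | 3.90 | 8 | 32% | 57% | 27% |

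**Step 4, check of the approximation.** An individual-level test estimates only the within-community variance, so the exact ratio of true to assumed variance is 1 + m × ICC/(1 − ICC): 1.303, 1.612, 2.579 and 4.333. With t and F reference distributions, pairwise type I error is then 8.5%, 12%, 22% and 34%, and four-arm type I error is 11%, 18%, 38% and 60%. Simulation with 20,000 runs per ICC gave 8.3%, 12.2%, 22.1% and 33.7% pairwise, and 11.0%, 18.0%, 38.0% and 60.4% for four arms. The type I errors in the table are therefore slightly low at the larger ICCs. Power by the normal approximation, at the matching back-solved d = 0.723, is 69%, 61%, 43% and 29%.

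**Step 5, more participants do not help.** As m grows, the effective n per arm cannot exceed 1/ICC: 100, 50, 20 and 10 for the four ICCs. The error degrees of freedom stay at 0.

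**The case against.** **The group-by-time test compares change, so community differences drop out.** Constant differences do, and for that reason the relevant ICC is that of change, which may be small. Differences in how communities change over time do not drop out.

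**The draw was random.** It was, at community level, for four units. That does not make this an individually randomized parallel-group trial, which is what the sample size presumes.

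**A full analysis plan may specify the clustering.** The article is silent on it and may leave it to a fuller document, so the point does not rest on that silence. A GEE clustered on the participant ignores the problem. One clustered on community has a single cluster per arm and no usable robust variance. The fault lies in the allocation.

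**The size is uncertain.** This stands. The ICC range and the reference effect are not in the article. The planned interaction over five time points has (4 − 1) × (5 − 1) = 12 df, so the four-arm column illustrates a single change score and is not the planned test itself.

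**Specific sources of community difference are conjecture.** Partly so. All arms follow one assessment schedule, and the article describes one intervention team for the training arms, so different seasons or staff should not be asserted. It is likewise only an inference that assessors working at a community's service centre could learn the arm of everyone there; the conclusion does not need it.

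**The limitations mention the small number of sites.** They do, but only for representativeness, not for confounding.

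**Conclusion.** The concern holds. That arm and community are completely confounded, with 0 degrees of freedom between communities within arms, follows from the article alone. So does the impossibility of reaching p < 0.05 on the randomization actually performed.

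The participant-level alpha and power are right only at an ICC of change of exactly 0, which the trial can neither test nor justify. At assumed ICCs of 0.01 to 0.10 with 30 per community, a nominal 5% pairwise test has a true error of about 8% to 32% (34% on the exact variance ratio). Power at the back-solved effect falls to between 69% and 27%. These sizes depend on the assumed ICC and effect; the main conclusion does not. The plan must be changed before between-arm results are presented as a powered randomized comparison.

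**What to change.** 1. In Sample size and Data analysis, withdraw the 0.05 alpha and 80% power claims for between-arm effects. In Study design and in Randomization, state that the allocation unit is the community, with one per arm, and that treatment effects are confounded with community. Remove the claim that random selection ensures comparability. Add the confounding to the limitations.

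2. Report arm differences as estimates and word the conclusions as non-confirmatory. Show intervals widened by √DE over a stated ICC range: factors of 1.14, 1.26, 1.57 and 1.97 at ICC 0.01, 0.02, 0.05 and 0.10. The exact ratio gives 2.08 at 0.10. These are sensitivity bounds that treat the ICC as known; they are not a cluster-level test.

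The cost of these two changes is protocol wording, matching registry wording where needed, and one sensitivity table. The claim becomes weaker. Both remain possible if allocation has already happened, as the past tense in the article suggests.

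3. If allocation has not been acted on, randomize individuals within each community, stratified by community, with community as a fixed factor in the GEE. This needs an amendment and delivery of all arms at every site, and it gives up some of the contamination control that the 5 km separation was meant to provide. The alternative is several communities per arm. As an illustration at d = 0.723, with 15 evaluable people per community and a pairwise cluster-level t test at 80% power, 4, 4, 5 or 6 communities per arm are needed at ICC 0.01, 0.02, 0.05 or 0.10. That is 16 to 24 communities in all.

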### Intervention group

The M-mBHT program was developed by a multidisciplinary team comprising nursing specialists, physiotherapists, psychologists, sociologists, and geriatricians. This team adhered to the ICFSR guidelines to design an integrated training program tailored specifically for older adults in rural communities [21]. The static-dynamic balance training component was derived from balance posture control movements [22], while the hand training component was designed by [name], a senior gymnastics coach in Shanghai, using principles of traditional Chinese medicine. The program follows a cyclic training mode, consisting of one week of instruction followed by one week of practice, facilitating steady skill acquisition and internalization by older adults. Training intensity progressively increases through altered sensory inputs and external distractions. The comprehensive program includes four parts: (1) a 5-10-minute warm-up session (including wrist, hip, shoulder, knee, and ankle range of motion exercises); (2) a 15-minute static balance training session (standing on both feet, tandem standing, and one-foot standing); (3) a 25-minute dynamic balance training session (normal gait, narrow gait, overlapping gait, and tandem gait); and (4) a 10-minute hand training session (finger exercises, acupuncture point stimulation, and finger relaxation phases). Detailed information is provided in Table 1. Based on the components of the comprehensive program, the three intervention groups are designated as follows: (a) Static Balance Training with Hand Training, (b) Dynamic Balance Training with Hand Training, and (c) multi-modal static-dynamic balance and hand function training (M-mBHF).

**Table 1 Tab1:**
[figure not shown]
Static balance training dynamic balance training and hand training programs

The intervention team comprised a sports professional, two general practitioners, three nurses, three community health workers, and four volunteer medical graduate students. The intervention program lasted 16 weeks, with sessions held twice weekly: one guided group session and one home-based independent exercise session using the same protocols listed in Table 1. Home exercises were self-administered by participants, but each intervention group was assigned to a dedicated WeChat group for remote supervision. Weekly instructional videos of training content were uploaded to the group chat, and research assistants provided online guidance to address execution errors or safety concerns. Participants self-monitored via WeChat video check-ins or exercise logs, allowing flexible adjustment of exercise intensity based on home environment conditions. Although direct in-person supervision was absent, the research team conducted weekly telephone follow-ups to monitor safety and protocol adherence, each lasting 50–60 min. Follow-up assessments were conducted at 8 and 16 weeks post-intervention.

Participants in all three intervention groups were instructed to maintain their daily lifestyles and avoid seeking any cognitively related information from external sources during the intervention period. They were also asked to report any changes in daily habits, including supplement and drug use, participation in recreational clubs, hospitalizations, and illness conditions. To mitigate potential risks associated with unsupervised exercise, all participants underwent baseline physical assessments and received detailed safety guidelines for home practice, including using stable furniture as support and emergency contact protocols. The multi-disciplinary team (including general practitioners) was accessible for urgent consultations to address health status changes promptly.

### Control group

The control group participated in a weekly 40-minute exercise health education session for 16 weeks. The curriculum covered routine exercises (including cardiovascular, flexibility, and resistance training), warm-up preparations, appropriate exercise duration, frequency, and intensity, exercise precautions, and fall prevention strategies during daily activities. These sessions were led by one health promotion professional and two community health workers. Follow-up assessments were also conducted at 8 and 16 weeks post-intervention.

